### Eligibility criteria

#### Diagnostic criteria

Participants will be diagnosed with MCI according to the 10th International Classification of Diseases (ICD-10) and 2018 Chinese guidelines for the diagnosis and treatment of dementia and cognitive impairment (V): diagnosis and treatment of MCI [14]; the main feature of MCI is the decline in cognitive function, which may include memory impairment and learning or concentration difficulties. Objective tests can often find abnormalities, but the symptoms do not meet the criteria for a diagnosis of dementia, organic amnesia syndrome or paranoia.

#### Inclusion criteria

Male and female participants are aged 60 years and older;Clear consciousness, normal hearing and visual abilities are maintained, and individuals have the ability to participate in the neuropsychological activity test;Participants meet diagnostic criteria for MCI in the ICD-10 and should meet the following items at the same time—the patient or participant subjectively feels that there is a decline in cognitive function, impaired cognitive function is noted in objective examination, and daily life function is basically normal;Participants do not meet the diagnostic criteria for dementia—the total score on the Clinical Dementia Rating Scale (CDR), Chinese version, is 0.0 to 0.5;The total score on the MoCA, Beijing version, is below 26 (years of education < 12 years, MoCA score < 25);Participants agree to sign the informed consent form and volunteer for this study.

#### Exclusion criteria

Participants with a history of mental disorders such as dissociative disorder, obsessive–compulsive disorder, personality disorder, schizophrenia, bipolar disorder, severe depression disorder, and anxiety disorder will be excluded.Participants with a history of drug or alcohol dependence or drug allergies will be excluded from this study.Participants who are taking antipsychotic medication or medications that affect cognition.Participants with a history of head trauma resulting in loss of consciousness will be excluded.Any participant for whom treatment was accepted in other clinical drug trials before the first study-drug administration and within 4 weeks of the present study will be excluded.Participants with serious gastrointestinal diseases (such as indigestion, gastrointestinal obstruction, or gastroduodenal ulceration) and serious secondary diseases that affect drug absorption will be excluded.Participants with hepatic and renal dysfunction, severe neurological diseases, cardiovascular and cerebrovascular disease complications and a history of other autoimmune diseases and any other contraindication were excluded.Participants with scores on the 30-item version of the Geriatric Depression Scale (GDS-30) higher than 20 will be excluded.Participants with a Hamilton Anxiety Rating Scale (HAMA, 14-item version) score ≥ 21 will be excluded.

#### Termination criteria

Patients who experience severe hepatotoxicity and nephrotoxicity related to drugs determined by the researchers during the study.Patients who experience other serious adverse events (AEs).Patients with comorbidities, complications or special physiological changes that may make them unsuitable for further study.Patients who use prohibited prescribed treatment.

#### Randomization

In this study, a stratified block randomization method will be used to divide the subjects in the same centre according to the "centre" first, and then subjects in the same centre will be divided into block randomization groups. This method not only ensures the balance of each known important prognostic factor but also ensures that the number of cases in each treatment group in each centre was close or equal; this method is also convenient for management. To ensure the comparability of the key factors affecting the prognosis of patients in the intervention or control group, the stratified factors considered in this study are centre, sex, age and TCM syndrome patterns. Block randomization requires that the research object of each block be a multiple of the number of groups (twofold or fourfold). The sample size of this experiment is 280 patients, so each group from each area should consist of 4 patients, for a total of 70 blocks. Among them, there were 35 (140/4) blocks from the Shanghai Municipal Hospital of TCM, 18 (70/4) blocks from Shanghai Jiading District Nanxiang Hospital, and 18 (70/4) blocks from the Shanghai Qingpu District Hospital of TCM. To reduce the loss of patients who meet the inclusion and exclusion criteria, the three centres could also set up a small number of blocks for 2 patients (such as fewer elderly patients) according to the actual needs.

At the same time, considering that when the three centres match patients of similar sex, age and TCM syndrome patterns into block groups, it is possible that the number of research objects in a block will be small or could lead to matching difficulties, so each centre should add 6 to 8 random participants (a total of 4 blocks).

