## Methods

### Study design

This study is a multicentre, randomized, double-blind, parallel-group, controlled trial. The objective of this trial is to evaluate the clinical efficacy and safety of YSF granules in elderly patients with MCI. The trial protocol (version 2.0, April 27, 2020) has been registered with the Chinese clinical trial registry (No. ChiCTR2000036807). The period for research recruitment is from August 5, 2021, to December 31, 2023. We present the following article in accordance with the SPIRIT 2013 reporting checklist. For more details about the checklist, please see Additional file 1.

Before the beginning of the clinical study, all researchers will be trained on the standardized process and scale evaluation consistency to ensure the clinical trial quality and data credibility of each centre. A total of 280 elderly patients with MCI will be randomly divided into a treatment group and a control group in a 1:1 allocation ratio. It will be carried out in three clinical centres in Shanghai, 140 subjects will be recruited at Shanghai Municipal Hospital of TCM, and we plan to recruit 70 subjects from Shanghai Qingpu District Hospital of TCM and 70 subjects from Shanghai Jiading District Nanxiang Hospital. All participants will experience a 1-week screening period, with an 8-week treatment period and follow-up visits at 24 and 48 weeks. The primary efficacy outcome measures will be the change in the Montreal Cognitive Assessment (MoCA) and Memory and Executive Screening (MES) scores, which will be used to assess cognitive function following the interventions. The TCM symptom scale is a combined measure of syndrome differentiation and treatment. Safety outcome markers will include hepatic and renal functions, electrocardiogram data, routine blood and urine test results, and severe clinical discomfort. The schedule of enrolment, interventions, assessments and data collection is presented in Table 1. The study will follow the Helsinki Declaration and the Good Clinical Practice guidelines. Ethical approval was granted by the Ethics Committee of Shanghai Municipal Hospital of TCM (approval no. 2020SHL-KY-06). Each subject could only be included in this study once and signed an informed consent form prior to study participation. The results of the study will help provide a clinical basis and TCM treatment plan for standardized diagnosis and treatment of MCI. The flowchart of this study is illustrated in Fig. 1.

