#### Blinding method

To control the bias caused by intentional or unintentional subjective factors in the process of clinical trials and the interpretation of results, neither the researchers nor the patients will know whether the test drug or the control drug was used by the patients. Eligible participants will be randomized to the treated group and control group at a 1:1 ratio. Twice unblinding will be used after data collection is completed. The data file will be locked after blinding verification and confirmation, and then the first unblinding will be performed. Data will be clustered to determine whether each number belongs to the A or the B group. The second unblinding will be performed after statistical analysis to determine whether group A or group B corresponds to the treated group or control group.

According to the abovementioned double-blind method, statistical experts will divide the drugs into two groups. Each participant will be assigned a medicine bag that contains all medication to be used during the treatment period. Each centre should distribute the drugs according to the drug number and the order of the subjects.

The research group will prepare an emergency letter for each subject. The envelope will be marked with the subject's drug number, and the inner sealed letter will indicate the subject's group, which will be used for emergency unblinding. The emergency envelopes will be saved at each centre and only opened for a clinical emergency. Once the blinded information is leaked or the opening rate of emergency letters exceeds 20%, the double-blind test is invalid. After sealing, blinded information will be delivered to the sponsor at Shanghai Municipal Hospital of TCM and managed by a specially assigned person.

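### The randomisation text names four stratification factors but lays out and counts blocks by centre only, and it lets recruiting centres shape the blocks

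*Protocol article*

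**What the plan says.** Under Study design, "A total of 280 elderly patients with MCI will be randomly divided into a treatment group and a control group in a 1:1 allocation ratio". For the lead site, "140 subjects will be recruited at Shanghai Municipal Hospital of TCM"; the target at each of the other two centres is 70.

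The Randomization section makes five statements that bear on this point:

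- Patients are separated by centre first and then randomised in blocks within centre.
- The stratification factors are centre, sex, age and TCM syndrome pattern. The method is said to guarantee balance on every known important prognostic factor. No age cut-off or number of patterns is given.
- Blocks hold 4 patients, "for a total of 70 blocks". The breakdown is 35 blocks at the lead hospital and 18 at each of the other two.
- To avoid losing eligible patients, "the three centres could also set up a small number of blocks for 2 patients", as actual needs dictate.
- Centres are described as matching patients of similar sex, age and pattern into blocks. Because that may be difficult, "each centre should add 6 to 8 random participants (a total of 4 blocks" in the article's count).

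The Blinding method section adds that statistical experts divide the drugs into two groups, that each participant has one medicine bag for the whole treatment period, and that "Each centre should distribute the drugs according to the drug number and the order of the subjects". Emergency envelopes showing the arm are kept at each centre. The Statistical analyses section names an independent two-sample t test for between-group comparisons of measurement data.

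**The concern.** Two different schemes are described as one. Blocks within centre need three sequences. Stratification by four factors needs a separate sequence for every combination of centre, sex, age class and pattern. The block counts belong to the first scheme; the list of factors and the balance claim belong to the second. A statistician preparing the lists, or a reader judging the trial later, cannot tell which was run.

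The provisions for matching and for blocks of 2 raise a separate matter. A randomisation list protects concealment because its structure is settled before patients are seen. Here the people who recruit may decide, with candidate patients in view, which patients form a block and when a block has only two places. The article also publishes both block sizes while recruitment is open.

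At stake are the balance claim, the predictability of some allocations, and a later account of how patients were allocated.

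**Working it through.** **1. Block counts.** Inputs: 280 patients, block size 4, centre targets 140, 70 and 70.

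- Total: 280 / 4 = 70, which reproduces the stated total.
- By centre: 140 / 4 = 35 and 70 / 4 = 17.5, rounded up to 18 at two centres. The sum is 35 + 18 + 18 = 71 blocks, or 71 × 4 = 284 places.
- Rounding down instead gives 35 + 17 + 17 = 69 blocks, or 276 places.
- Seventeen blocks of 4 plus one block of 2 at each smaller centre gives exactly 17 × 4 + 2 = 70 patients there, but still 71 blocks in all.

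No variant gives 70 blocks with this breakdown.

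**2. Reserve.** 3 × 6 = 18 to 3 × 8 = 24 patients.

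- In blocks of 4: 18 / 4 = 4.5 to 24 / 4 = 6 blocks.
- Four blocks of 4 for the whole trial is 16 places, fewer than 18.
- Four blocks of 2 per centre is 8 places, the top of the range. The bottom, 6, would be three blocks of 2.

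If the reserve were used in full, the total would be 280 + 18 = 298 to 280 + 24 = 304, or 302 to 308 starting from 284.

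**3. Number of strata.** Assume two age classes and two patterns, the smallest possible case: 3 × 2 × 2 × 2 = 24 strata.

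- Mean stratum size: 280 / 24 = 11.7 overall and 70 / 8 = 8.75 in each smaller centre.
- If stratum sizes leave remainders 0, 1, 2 or 3 about equally often after division by 4, three quarters of strata end in an unfinished block: 24 × 0.75 = 18. With three patterns there are 36 strata and 36 × 0.75 = 27 unfinished blocks. Simulation gave the same values (18 and 27).

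The article's counts by centre make no provision on this scale.

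**4. Balance if only centre is stratified.** Assume a factor present in 50% of patients and arms of 140.

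- SE of the difference in proportions = √(0.25 × 2 / 140) = 0.0598.
- P(gap ≥ 10 points) = 2 × [1 − Φ(0.10 / 0.0598)] = 2 × [1 − Φ(1.67)] = 0.094.
- Ten points is 14 patients. Counting whole patients exactly (binomial with 280 trials, at least 14 from the mean of 140) gives 0.106, so the answer is 9% to 11% per factor.
- A smaller gap, 10 or more patients of one sex, occurred in about 25% to 27% of 3,000 simulated trials under centre-only blocks of 4. With blocks within all four factors the figure was 0.2% to 6.4%, depending on whether 2, 3 or 5 equally frequent patterns were assumed.

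**5. Predictability.** In a 1:1 block of 4, once the first arm is known, two of the three remaining places are the other arm, so the next guess is right with probability 2/3. In a block of 2 the remaining place is certain.

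**The case against.** The strongest defence is that the dispensing sentence refers to drug number and the order of subjects, not to order of enrolment. Drug numbers could be allotted in ranges by stratum, and the sentence would still be true. A journal article may leave the layout of kit lists to the full protocol. The blocks of 2 and the reserve also suggest that the authors foresaw sparse strata. This stands: a reader might infer that kits are certainly handed out in one queue per centre and that balance certainly fails, and the text does not establish that. It does not remove the conflict between four named factors and blocks laid out by centre, which is stated and not merely omitted.

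A reader might also infer that sites control allocation. They do not choose the arm: statisticians divide the drugs, bags are numbered, researchers and patients are blinded, and the control granules are made to look and taste similar. Knowing that a block has two places helps only someone who already knows or guesses the first arm, and envelopes are reserved for emergencies. What stands against the plan is the narrower point that block structure is open to site decisions.

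The matching and centre-only readings cannot both hold. If centres really do match on sex, age and pattern, balance on those factors improves and the 9% figure does not apply; if they do not, the matching text is wrong.

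Finally, a 10-point gap is ordinary chance imbalance under valid randomisation. If the factor moved MoCA by 0.5 to 2 points (an assumption; the article gives no figure), the gap would shift the group difference by 0.10 × 0.5 = 0.05 to 0.10 × 2 = 0.2, against the 25.67 − 23.36 = 2.31 assumed in the sample size section. That is accepted: the imbalance is neither bias nor a threat to the test.

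**Conclusion.** The randomisation text is internally inconsistent and should be corrected. Four stratification factors imply at least 24 strata (binary age and pattern assumed), while blocks are laid out and counted for three centres. Unless stratum-specific kit ranges exist, the guaranteed balance is not delivered beyond centre, with a 9% to 11% chance of a gap of 10 points or more for any one factor split 50/50. That size depends on the assumed split and describes chance variation only.

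The permission for centres to match patients into blocks and to create blocks of 2 means the structure is not fixed in advance. The consequence is some added predictability after an unblinding, not site choice of treatment.

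The 71 versus 70 discrepancy is a rounding slip of four places and minor alone. The reserve might be read as a plain arithmetic error, but it can be reconciled as four blocks of 2 per centre, so it is ambiguous rather than demonstrably wrong.

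**What to change.** - Have the statistician issue all remaining sequences centrally, with block sizes fixed beforehand and not disclosed to the centres.
- Delete the permission for centres to set up blocks of 2 and the text on centres matching patients into blocks.
- State one scheme: either stratification by centre only, dropping the claim of guaranteed balance on other factors, or stratum-specific kit sequences with the age classes and patterns defined.
- Adjust the primary between-group comparison for centre, sex, age and syndrome pattern instead of relying on the two-sample t test alone. This deals with chance imbalance under either scheme.
- Correct the counts: 71 blocks (284 places) if full blocks of 4 are used, and state the reserve with its block size and whether it is per centre or for the trial.
- Record which scheme was applied to patients already randomised, including any blocks of 2.

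Cost: a short amendment and re-listing of unissued kits. The re-listing carries a blinding risk of its own, so only unblinded staff should handle it. No extra patients are needed, and the article reports recruitment as still in progress.

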#### Blinding method

To control the bias caused by intentional or unintentional subjective factors in the process of clinical trials and the interpretation of results, neither the researchers nor the patients will know whether the test drug or the control drug was used by the patients. Eligible participants will be randomized to the treated group and control group at a 1:1 ratio. Twice unblinding will be used after data collection is completed. The data file will be locked after blinding verification and confirmation, and then the first unblinding will be performed. Data will be clustered to determine whether each number belongs to the A or the B group. The second unblinding will be performed after statistical analysis to determine whether group A or group B corresponds to the treated group or control group.

According to the abovementioned double-blind method, statistical experts will divide the drugs into two groups. Each participant will be assigned a medicine bag that contains all medication to be used during the treatment period. Each centre should distribute the drugs according to the drug number and the order of the subjects.

The research group will prepare an emergency letter for each subject. The envelope will be marked with the subject's drug number, and the inner sealed letter will indicate the subject's group, which will be used for emergency unblinding. The emergency envelopes will be saved at each centre and only opened for a clinical emergency. Once the blinded information is leaked or the opening rate of emergency letters exceeds 20%, the double-blind test is invalid. After sealing, blinded information will be delivered to the sponsor at Shanghai Municipal Hospital of TCM and managed by a specially assigned person.

### Interventions

#### Intervention group

YSF granules (4.24 g/bag, batch number: 201007) are provided by Sichuan Neo-Green Pharmaceutical Technology Development Co., Ltd., which is one of only six TCM formula granule manufacturers approved by the China Food and Drug Administration (Production Licence Number: Chuan 20,160,134). The components of YSF granules are listed in Table 2. Two bag granules will be added to 200 ml of warm water and administered orally every morning and evening after meals for 8 weeks. The granules should be stored at room temperature in a dry and dark location out of reach of children.

**Table 2 Tab2:** Overview of Yi Shen Fang

	Chinese medicine	Family	Amount (%)	TCMH action
1	Xiangfu (*Cyperus rotundus*)	Cyperaceae	21.13%	Soothe the liver, regulate qi, and regulate menstruation to relieve pain
2	Rougui (*Cinnamomum verum*)	Lauraceae	4.23%	Tonify fire and assist yang, direct fire back to its origin, dissipate cold to relieve pain, and activate blood to unblock the meridians
3	Sharen (*Amomum dealbatum*)	Zingiberaceae	8.45%	Resolve dampness to move qi, warm the middle to inhibit diarrhoea, and prevent miscarriage
4	Shanzhi (*Gardenia jasminoides*)	Rubiaceae	12.68%	Purge fire to except vexed clear heat and drain dampness, cool the blood and detoxify, and disperse swelling and relieve pain
5	Shichangpu (*Acorus calamus*)	Acoraceae	12.68%	Resolve phlegm to open the orifices, resolve dampness and harmonize the stomach, nourish the heart and tonify intelligence
6	Yuanzhi (*Polygala tenuifolia*)	Polygalaceae	12.68%	Tranquillize the patient, tonify intelligence, and resolve phlegm to open the orifices
7	Xuancaohua (*Hemerocallis lilioasphodelus*)	Asphodelaceae	28.17%	Clear heat, drain dampness, and cool the blood to stop bleeding

*TCMH* traditional Chinese medicine herb

#### Control group

The control group will receive granules with a 10% drug concentration (0.42 g/bag) serving as the placebo [15], which the ingredients and the preparation process are the same as the YSF granules (Table 2). Following the principle of a double-blind trial, food colorants and flavouring agents will be added so that the two groups of drugs can be similar in terms of colour, smell, taste and quality. The usage is the same as above.

#### Drug combination

During the study period, no cognitive improvement drugs will be allowed. All combined drugs should be recorded in a case report form (CRF), including the drug name, production batch, usage and dosage, course of treatment, treatment plan and other related information. During the trial, the concurrent use of other TCM preparations will not be allowed. Finally, the researchers will determine whether the participants should withdraw from the study according to the combined drug usage.

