**Methods:**

This study is a multicentre, randomized, double-blind, parallel-group, controlled trial. Based on the results of previous clinical trials, 280 elderly patients with MCI will be randomly divided into a treatment group (*n* = 140) and control group (*n* = 140). The study will last 33 weeks, including 1 week of screening, 8 weeks of intervention, and 24 weeks of follow-up. The primary outcomes will be the changes in Montreal Cognitive Assessment (MoCA) and Memory and Executive Screening (MES) scores before and after the intervention. The secondary outcome measures will be homocysteine (HCY) levels, Functional Assessment Questionnaire (FAQ) scores and event-related potential (ERP) detection in typical cases. The TCM symptom scale is a combined measure of syndrome differentiation and treatment. During this study, the classifications and characteristics of adverse events, the times of occurrence and disappearance, the measures of treatment, their impact on the primary disease, and outcomes will be reported truthfully.

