#### Primary outcomes

Cognitive status will be evaluated with the MoCA and MES. The primary efficacy endpoints are the improvement rate for MoCA scores and MES scores, which will be measured before and after treatment in both groups. The MoCA has high sensitivity and specificity in distinguishing normal elderly individuals from those with MCI and mild Alzheimer's disease and can detect slight cognitive impairment [16]. The MES has been confirmed to be a valid and easily administered screening tool for MCI, and the score is independent of education and can also be used to evaluate individuals [17].

$$\text{Improvement rate} = \left[\left(\text{posttreatment score}-\text{pretreatment score}\right)/\text{pretreatment score}\right]\times100\%.$$

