### Statistical analyses

In this study, the data analysis will be performed on the full analysis set (FAS), per protocol set (PPS) and safety analysis set (SS). The efficacy analysis will be conducted on an intention-to-treat (ITT) basis. The 95% confidence intervals (CIs) will be calculated as exact CIs. For the two primary outcomes, the *P*-value will be adjusted to 0.033. This value was based on a recommendation to divide the pre-specified *P*-value threshold by the value halfway between 1 (representing no adjustment) and the number of primary outcome comparisons (the denominator used for the Bonferroni correction) [23]. All statistical tests are 2-sided, and unless otherwise stated, *P* < 0.05 will be considered statistically significant. When the primary outcome measures are missing, the researchers will combine statistical analysis and clinical experience to judge whether to exclude the subject or replace the missing data with the last observation carried forward (LOCF).

The measurement data will be subject to normal distribution and homogeneity of variance, which is expressed as the mean ± standard deviation. Comparisons between groups will be performed using an independent 2-sample t test. Comparisons between multiple time points will be analysed using repeated-measures ANOVA, multivariate ANOVA or paired t test. When the data do not meet the criteria of normality and homogeneity, the results will be expressed as the median. The Wilcoxon rank sum test will be used to compare differences between groups. Before and after treatment, numerical variables and ordered categorical variables measured over multiple time points will be analysed using generalized estimating equations and a mixed effects model. The enumeration data will be expressed as frequency (n), constituent ratio (%) or ratio (%). If the variable data type is unordered, categorical comparisons between groups will be performed by the χ^2^ test. The ordered categorical variable data will be analysed using the rank sum test. Comparisons of two-way ordered data with different properties within contingency tables will be made with the linear chi-square test or rank sum test. Multivariate data analysis will be conducted using multiple linear regression, the K-M test, Cox regression or a trend test. All statistical analyses will be performed with IBM SPSS Statistics 24.0.

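### Concomitant-drug use can remove a patient from the study, not just from the granules, and the missing-data rule then allows exclusion despite the ITT statement

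*Protocol article*

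**What the plan says.** All references are to the protocol article.

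- **Drug combination** sets the ban: "During the study period, no cognitive improvement drugs will be allowed". Other TCM preparations are banned too. Concomitant drugs go into the CRF, and then "the researchers will determine whether the participants should withdraw from the study according to the combined drug usage".
- **Termination criteria** lists "Patients who use prohibited prescribed treatment" as a ground for termination. It does not say whether visits continue afterwards.
- **Abstract, Methods** gives the length: "The study will last 33 weeks, including 1 week of screening, 8 weeks of intervention, and 24 weeks of follow-up". Table 1 places its follow-up columns (weeks 12 and 24) under the same study-period heading as the treatment columns.
- **Intervention group** says the granules are "administered orally every morning and evening after meals for 8 weeks".
- **Exclusion criteria** keeps out current users: "Participants who are taking antipsychotic medication or medications that affect cognition".
- **Primary outcomes**: "The primary efficacy endpoints are the improvement rate for MoCA scores and MES scores", as percentage change from before to after treatment.
- **Statistical analyses** puts efficacy on an ITT basis. In the same paragraph, when a primary outcome is missing, researchers use statistical analysis and clinical experience to "judge whether to exclude the subject or replace the missing data with the last observation carried forward (LOCF".

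**The concern.** Two discretionary steps can follow one another. A researcher may take a patient out of the study because of a concomitant drug. If the week-8 scores are then not collected, someone judges whether the patient leaves the analysis or has an old score carried forward. Neither step has a fixed rule.

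Starting a cognition drug may well reflect how the patient is doing. If it does, the patients lost are selected on outcome after randomisation, and the estimated difference can be biased in either direction. A later analysis plan can choose a better missing-data method, but it cannot recover scores that were never collected. The remedy therefore belongs in the protocol.

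**Working it through.** **1. What withdrawal ends.** Before week 8 the wording is ambiguous: leaving the study could loosely mean stopping the granules. After week 8 it is clearer. The granules have ended, yet the ban appears to continue through follow-up. A patient who starts a cognition drug then has no study drug to stop, so withdrawal can only end the remaining visits (weeks 12 and 24 in Table 1).

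**2. The conflict.** ITT keeps every randomised patient in the efficacy analysis. Excluding a patient because the primary outcome is missing does not. Carrying a score forward keeps the patient in, so the contradiction is confined to the exclusion option.

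**3. The plan's own figure.** From Sample size calculation, MoCA means are 25.67 and 23.36, margin 1.20, SD 2.21, z-values 1.96 and 1.645:

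n = (1.96 + 1.645)² × 2.21² × 2 / (25.67 − 23.36 − 1.20)² = 12.996 × 4.884 × 2 / 1.232 = 103.03, rounded up to 104 per group.

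This equals the stated 104. On these inputs at two-sided 0.05, power is 0.988 with 140 per group and 0.964 with 112 (20% lost). The issue is selective loss, not loss of power.

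**4. Bias on raw MoCA.** The document gives no termination rate. Assume 5% (14 of 280), leaving 266, or 133 per arm. Planned difference d = 2.31. Standard error = 2.21 × √(2/133) = 0.27.

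| Mechanism, terminated patients excluded | Removed, treated / control | Bias (points) |
|---|---|---|
| (i) Terminated patients would show no difference | 5% / 5% | +0.05 × 2.31 = +0.12 |
| (ii) One cut-off (20.41) removes the lowest scorers | 0.9% / 9.1% | -0.35 |
| (iii) Removal correlates 0.5 with score (simulated) | 2.5% / 7.5% | -0.10 |

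For (ii), the means of normal distributions truncated at 20.41 are 25.72 (treated) and 23.76 (control). Their difference is 1.96, and 1.96 − 2.31 = -0.35.

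With half the effect (d = 1.155), (ii) gives -0.21 and (iii) -0.06. With d = 0, each arm loses 5.0% and the bias is 0 in all three.

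**5. LOCF instead of exclusion.** With equal rates by arm, bias = 0.05 × (carried-forward difference − true week-8 difference in the terminated). If each lies between 0 and 2.31, the bias lies between -0.12 and +0.12.

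**6. The actual primary endpoint.** Percentage improvement was simulated with assumed mean baseline MoCA of 20 to 22, baseline SD 2.21 and pre-post correlation 0.5 to 0.8. A baseline mean of 24 is left out. On a normal model it puts about 18% of patients at 26 or above, where Inclusion criteria bars entry.

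- Difference between arms: 10.6 to 11.7 percentage points.
- (i): 0.05 × 10.6 to 0.05 × 11.7 = +0.5 to +0.6.
- (ii), lowest improvers removed: -1.2 to -1.8, about 11 to 15% of the difference.
- (iii): about -0.4, roughly 3 to 4% of the difference.
- With no treatment effect: 0.

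**The case against.** **The defect is in the missing-data rule.** The only outright contradiction lies inside Statistical analyses and applies to missing data from any cause. That is true of the contradiction. The withdrawal wording, however, is a separate stated rule that creates missing data, and a better analysis rule alone would not restore the scores.

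**Nothing says that assessments stop.** A journal article may leave post-withdrawal visits to the full protocol. This stands for the period before week 8, which is why the point is conditional there. But the article does state the withdrawal rule, the termination ground and the exclude-or-LOCF rule, so the complaint concerns what is written.

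**The clear case and the harmful case differ.** The wording is clearest in follow-up, when the primary endpoint has already been measured. Before week 8, current users are already excluded, so only new starts within eight weeks matter. This is correct and limits the effect on the primary endpoint. The follow-up reading also leans partly on a table heading.

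**Blinding and size.** Researchers are blinded and cannot knowingly withdraw by arm. Drug use driven by response can still differ between arms. The -0.35 case needs removal fully determined by score and is an extreme. The moderate cases are under half a standard error.

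**Conclusion.** The concern holds. As written, the rules can take a randomised patient out of the study at a researcher's discretion because of concomitant drug use. If the primary scores are then missing, they allow exclusion in conflict with the stated ITT analysis. Before week 8 this depends on withdrawal also ending assessments, which the text leaves open.

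The true size and direction cannot be known from the document. At an assumed 5% terminated, plausible bias on raw MoCA is about a tenth of a point either way, with an extreme of -0.35 against a planned difference of 2.31. The 24-week follow-up leaves more time for new starts than the eight treatment weeks. The mechanisms shown distort the size of a real effect and do not produce a false positive. The change should be made, with medium confidence about its practical effect.

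**What to change.** 1. In Drug combination and Termination criteria, state that prohibited-drug use, or meeting a termination criterion, ends study drug only.
2. Continue MoCA, MES and FAQ at the scheduled visits, including follow-up, unless the patient withdraws consent.
3. In Statistical analyses, keep all randomised patients in the FAS, and state that termination or prohibited-drug use is not a ground for exclusion.
4. Use the CRF record of concomitant drugs to handle prohibited-drug use in the PPS or a sensitivity analysis.

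The cost is a few sentences of protocol wording and already scheduled visits for a few off-drug patients. The downside is a slightly diluted estimate, because scores after stopping the granules or starting a cognition drug are included. Trial status reports recruitment still in progress, so an amendment could protect data not yet collected at that time.
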